**Methods:**

The study is an open-label cluster-randomized effectiveness-implementation hybrid trial including all 78 cardiac rehabilitation centres (attending to approximately 10 000 MI patients/year) that report to the SWEDEHEART registry. The centres will be randomized 1:1:1 to three clusters: 1) reporting cardiac rehabilitation structure and process variables to SWEDEHEART every six months (audit intervention) and being offered implementation support to implement guidelines on secondary prevention (implementation support intervention); 2) audit intervention only; or 3) no intervention offered. Baseline cardiac rehabilitation structure and process variables will be collected. The primary outcome is an adherence score measuring centre-level adherence to secondary prevention guidelines. Secondary outcomes include patient-level secondary prevention risk factor goal attainment at one-year after MI and major adverse coronary outcomes for up to five-years post-MI. Implementation outcomes include barriers and facilitators to guideline adherence evaluated using semi-structured focus-group interviews and relevant questionnaires, as well as costs and cost-effectiveness assessed by a comparative health economic evaluation.

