### Randomization

Centres will be randomized 1:1:1 to three clusters (A, B and C). Randomization will be stratified by geographical healthcare district (two districts in each stratum). Randomization will be performed by an independent organisation not involved in the study to avoid site-selection bias.

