### Secondary effectiveness outcomes

Table 2 displays secondary outcomes, encompassing both short- and long-term patient outcomes and implementation outcomes. Implementation outcomes will be based on responses gathered through the customized Normalisation Measure Development (NoMAD) questionnaire [29] and insights obtained from focus group interviews, as well as a cost-effectiveness analysis.

**Table 2 Tab2:** Secondary outcomes

Outcomes	Cluster	Measures	Data source	Timing
Short-term patient-level outcomes	All clusters	- Blood pressure (mmHg). - LDL-C (mmol/L). - Self-reported statue of health measured using EuroQol-VAS (0–10). - Self-reported smoking status (never/ prior [> 1 month smoke-free]/active) - Self-reported dietary habits (four questions with Likert scale 0–3 points, total score 0–12 points). - Self-reported physical activity (the number of days during the last week the patient has been physically active for a minimum of 30 min [at least 10 min at a time] with activity causing shortness of breath and a slightly increased pulse, corresponding to a brisk walk). - Completing an exercise-based CR programme for at least 3 months (yes/no)	The SWEDEHEART registry	Baseline and one-year after the start of intervention
		- Adherence to secondary prevention medication	Pharmaceutical registry	Baseline and one-year after the start of intervention
Long-term patient-level outcomes	All clusters	Total mortality Major adverse cardiovascular events (MACE) consisting of the following: - cardiovascular mortality - non-fatal MI - non-fatal ischemic stroke - coronary revascularization - hospitalization for new or worsening heart failure	National Patient Registry and the Cause of Death Registry	Up to 5 years after the end of the intervention
Centre-level implementation outcomes	Cluster A	- Barriers - Facilitators	Semi-structured focus group interviews	At the start and the end of implementation support period
		- Implementation cost and cost effectiveness.	A comparative health economic evaluation	At the start and the end of implementation support period

*LDL-C* low-density lipoprotein cholesterol, *VAS* visual analogue scale, *CR* cardiac rehabilitation, *MI* myocardial infarction

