### Sample size calculations

As the number of CR centres is fixed, sample size calculations have been performed to estimate the difference in mean adherence score the study will be able to reveal. For this purpose, in a feasibility analysis the CR structure and process variables were collected from 8 CR centres of different sizes and geographical locations. The mean adherence score was 30.8 (standard deviation [± 2.4]) out of a maximum available score of 39. For the audit intervention, given the following presumptions:

23 out of possible 26 CR centres in each group (minimal drop-out is anticipated).Power of 80%.An alpha value of 0.05.

The study will have the power to identify a difference of ± 2.0 in adherence score between centres in cluster B (randomized to having variables on CR structure and processes incorporated in the SWEDEHEART registry) and cluster C (no new variables incorporated).

For the implementation support intervention, only centres in the lower 2 tertiles of the adherence score at baseline (approximately 17 centres) will be offered implementation support. Given the following presumptions:

14 out of possible 17 centres in each group (minimal drop-out is anticipated).Power of 80%.An alpha value of 0.05.

The study will have the power to identify a difference of ± 2.5 in adherence score between centres in cluster A (randomized to receiving implementation support) and cluster B (no implementation support).

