### The timeline

The audit intervention started in October 2023 and will continue for 3 years. An interim analysis will be conducted two years after the start of the intervention. If the interim analysis shows the primary endpoint to be met (a difference of at least ± 2.0 in adherence score) the intervention will be terminated. Otherwise, the intervention will be continued until October 2026 and thereby uphold.

The implementation support intervention will start Q2 2024. Centres randomized to the implementation intervention will receive implementation support consecutively over a period of 18 months. The order in which centres will receive implementation support will depend on the centres’ possibilities and the research team´s capacity. The study outline is displayed in Table 3.

**Table 3 Tab3:** Flow chart for the study

**Procedure**	2023		2024		2025		2026		2030
	Q3	Q4	Q1-2	Q3-4	Q1	Q3	Q1	Q3	
Randomization	√								
Structure and process variables - intervention sites (cluster A and B)	√	√	√	√	√	√	√	√	
Interim analysis						√			
Implementation support at intervention sites (cluster A)			√	√	√				
Utility of implementation assessment (cluster A)			√	√	√				
Structure and process variables -control sites (cluster C)	√					√		√	
End of audit intervention						(√)		√	
End of follow-up									√

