### Data analysis

In the primary outcome analysis of the audit intervention, CR centres in clusters B and C will be compared. All CR centres that have responded to the CR structure and process variables will be included in the analysis. For the primary outcome analysis of the implementation support intervention CR centres in clusters A and B will be compared. All CR centres that have i) provided answers to the structure and process variables and that ii) have scores in the lower two tertiles of the adherence score at baseline will be compared. Our analyses will assume intention-to-treat principles by treating intervention assignment as randomized regardless of whether the intervention had uptake within the practice. If not all centres in cluster A accept implementation assistance, a per-protocol analysis will be performed including only those centres in study group A that accept implementation assistance.

For the secondary analyses on patient outcomes, all patients that attended at least two follow-up visits within CR will be included. For the outcome analysis of the audit intervention patients followed at CR centres in clusters B and C will be compared. For the outcome analysis of the implementation support intervention patients followed at CR centres in clusters A and B will be compared. A per-protocol analysis will be performed including only patients belonging to CR centres in cluster A that accept implementation assistance.

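### The patient-level A-versus-B comparison drops the lower-two-tertile restriction, so about a third of cluster A centres in it are never offered support; its short-term read-out date is also undefined

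*Protocol article*

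**What the plan says.** **Who is offered support.** The 78 centres are allocated 1:1:1, about 26 per cluster. Under Sample size calculations, "only centres in the lower 2 tertiles of the adherence score at baseline (approximately 17 centres) will be offered implementation support".

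**Primary A-versus-B analysis.** Under Data analysis, the centres compared are those that answered the structure and process variables and that "have scores in the lower two tertiles of the adherence score at baseline will be compared". The limit applies to both clusters.

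**Patient-level A-versus-B analysis.** The next paragraph of the same section sets the population: "For the secondary analyses on patient outcomes, all patients that attended at least two follow-up visits within CR will be included". It then sets the contrast: "For the outcome analysis of the implementation support intervention patients followed at CR centres in clusters A and B will be compared". No tertile limit is stated. A per-protocol analysis limits cluster A to centres that accept assistance and states no corresponding limit on cluster B.

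**Timing.** Table 2 reads short-term patient outcomes, for all clusters, at "Baseline and one-year after the start of intervention". The abstract instead speaks of "patient-level secondary prevention risk factor goal attainment at one-year after MI". Under The timeline, the audit started in October 2023, support starts in Q2 2024, and cluster A centres "will receive implementation support consecutively over a period of 18 months". The section on the implementation support intervention sets the start separately for each centre once it accepts.

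**The concern.** The two A-versus-B populations stand in adjacent paragraphs and do not match. The primary one follows the rule on who is offered support. The patient-level one, as written, brings back the top-tertile centres, whose cluster A members are excluded from support by design. Their patients count as support patients, and any effect is averaged with a group in which none is expected.

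The secondary aim on whether support improves patient outcomes rests on this comparison. So does the patient-outcome part of the cost-effectiveness analysis, which uses the effect of the assistance on patients.

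The second issue is the date of the short-term read-out. Support reaches centres one after another, so the share of cluster A exposed at the read-out depends on which start is meant. The article does not say.

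**Working it through.** **1. The plan's own figures.** No patient-level sample size is stated, so only the adherence-score figures can be reproduced. The inputs from Sample size calculations are SD 2.4, 80% power and alpha 0.05 (two-sided, from Quantitative data). Detectable difference = (1.960 + 0.842) × SD × √(2/n).
- B versus C, n = 23: 2.802 × 2.4 × √(2/23) = 1.98 (stated 2.0).
- A versus B, n = 14: 2.802 × 2.4 × √(2/14) = 2.54 (stated 2.5).

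Both reproduce. The A-versus-B figure is built on the restricted set (14 of a possible 17), so the design calculation already treats that set as the relevant one.

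**2. Share of cluster A never offered support.** 26 × 2/3 = 17.3, so about 17 are offered and about 9 are not; 9/26 = 35%.

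**3. Attenuation.** Let d be the effect in offered centres, and assume no effect elsewhere and equal patients per centre. The all-centre effect is (17/26) × d = 0.654d. The top tertile's share of patients is not given. If it is 20%, the factor is 0.80; if 50%, it is 0.50.

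**4. Do the extra centres compensate?** With n equal-sized centres per cluster, the signal-to-noise ratio is proportional to effect × √n.
- Restricted: d × √17 = 4.12d.
- All centres: 0.654d × √26 = 3.33d.
- Ratio, all to restricted: 3.33/4.12 = 0.81 (the inverse is 1.24).

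If the restricted comparison has 80% power, its standardised effect is 1.960 + 0.842 = 2.802. With all centres it is 2.802 × √(17/26) = 2.266, and the power is Φ(2.266 − 1.960) = 0.62. In information terms the restriction gains 26/17 = 1.53-fold.

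**5. Exposure at the short-term read-out.** Assume centres start evenly over the stated 18 months, with the first start between the beginning of April and the end of June 2024.

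| Meaning of start of intervention | Read-out | Offered centres that have started |
|---|---|---|
| Audit start, October 2023 | October 2024 | 3/18 to 6/18 = 17% to 33% (about 3 to 6 of 17) |
| Support start, Q2 2024 | Q2 2025 | 12/18 = 67% (about 11 of 17) |
| Each centre's own start | centre-specific | all supported centres; no counterpart date in B |

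Table 3 ticks support only to Q1 2025. If that marks a roll-out of about 12 months, the first row becomes 3/12 to 6/12 = 25% to 50%, and in the second row all offered centres have started.

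**The case against.** **The omission may be one clause lost in a condensed article.** That is possible. But the article states both populations side by side, with the limit in one and not in the other. If the limit is meant, a clause settles it.

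**Comparing all of A with all of B follows intention-to-treat.** This stands. It is a valid randomised estimate of assignment to A versus B. But the tertile limit uses a baseline variable in both clusters, so the restricted comparison also keeps the randomisation, and the primary analysis already uses it.

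**The per-protocol analysis removes the centres that were never offered support.** It does so in cluster A only. As no matching limit on B is stated, lower-tertile accepting centres in A would face B centres from the whole range of baseline adherence. Dilution would be exchanged for baseline imbalance.

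**Stronger readings that the document does not support.**
- *The read-out comes before most centres receive support.* Two things favour the audit start: Table 2 applies to all clusters, and The timeline counts the interim analysis from the audit start. But the intervention tested in A versus B is support. Counted from Q2 2024, about two thirds of offered centres have started, and on a centre-specific start the timing dilution disappears. The established fault is an undefined anchor.
- *Patients with an MI around October 2023 are unexposed.* Their rehabilitation runs to a one-year visit, so part of it could fall under support.
- *The comparison is largely unexposed, or a null result would say nothing.* About 65% of cluster A centres are offered support. The result would be attenuated, not empty.
- *The cost is 2.3-fold information (1/0.654² = 2.34).* That holds the number of centres at 26. The choice available is 26 diluted against 17 undiluted, and the net factor is about 1.5.
- *The whole cost-effectiveness analysis is affected.* It also uses guideline adherence, for which the primary comparison is restricted.

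**Conclusion.** The population mismatch holds. As written, the patient-level A-versus-B analysis includes about 9 of 26 cluster A centres that cannot be exposed. It attenuates the effect in offered centres to about 0.65 (0.50 to 0.80 if unoffered centres hold 50% to 20% of patients) and lowers 80% power to about 62%. The power figure assumes equal centre sizes, the same variability in both sets and no effect in unoffered centres. The mismatch affects both short- and long-term patient outcomes.

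The timing point holds only as an inconsistency: Table 2 does not say which start it means, a centre-specific start has no counterpart in cluster B, and the abstract counts from the MI. The figure of 17% to 33% of offered centres started applies only if the audit start is meant and the roll-out is even over 18 months. It does not concern the long-term outcomes, which run up to five years after the intervention ends.

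**What to change.** 1. Make the main patient-level A-versus-B analysis, for short- and long-term outcomes, the patients at centres in the lower two baseline tertiles in both A and B, with the same cut-offs as the primary analysis. Keep the all-centre comparison as a sensitivity analysis.
2. If the per-protocol analysis stays, state which cluster B centres it uses, and limit them at least to the same tertiles.
3. Reconcile Table 2 with the abstract. For A versus B, define an anchor tied to the support roll-out and give cluster B centres a matching date, fixed without reference to outcomes.

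The cost is mainly wording. Baseline scores are collected at all centres, so no new data are needed for the restriction. The main analysis has fewer patients (about 17 instead of 26 centres per cluster), and its result applies to centres in the lower two tertiles. Centre start dates must be recorded for the anchor.

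Admitting only MI discharges after the roll-out is complete is not advised. Eighteen months from Q2 2024 ends at about Q4 2025, so one-year visits would begin at about Q4 2026. That is at or past the planned end of the audit intervention in October 2026, and all patients treated during the roll-out would be lost.

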### Quantitative data

For baseline characteristics descriptive statistics will be used (means +/-standard deviation, medians [quartile 1, quartile 3], proportions [%] and ranges). For the primary outcome analysis, given randomized treatment assignment, total adherence scores at end of follow-up as well as change in scores between baseline and follow-up will be compared using linear regression analysis. In the case of unequal randomization concerning CR centre size (small < 75 patients/year, medium 75–150 patients/year or large > 150 patients per year), geography (6 geographical districts in Sweden, two in each stratum) or the centres belonging to a university hospital (yes/no), adjusted multivariable analysis will be performed. Results will be reported as relative treatment effects (odds ratios) with 95% confidence intervals. For secondary outcome analysis on short-term patient outcomes, the same statistical methods will be used, applying linear (continuous) or logistic (binary) regression analyses. For long-term outcomes (major adverse cardiovascular events [MACE] and total mortality) Cox proportional hazards regression models will be performed, reporting hazard ratios with 95% confidence intervals. In case of missing data, imputation will be considered. For all quantitative analyses a two-sided test of statistical significance will be used with an alpha level of 0.05.

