### The interventions

First, baseline structure and process variables will be administered through the SWEDEHEART-CR registry at all CR centres. Second, two clusters will receive one of two interventions (A and B) and one cluster will receive no intervention (control cluster) (C) (Fig. 1):

A)Reprting CR structure and process variables through the registry every six months and being offered structured implementation support (audit intervention + implementation support intervention).B)Reporting CR structure and process variables through the registry every six months but no structured implementation support being offered (audit intervention).C)No reporting of CR structure and process variables, and no structured implementation support offered (control).

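### Two unranked primary contrasts per comparison, final score and change score, where one baseline-adjusted regression would give a single and more precise result

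*Protocol article*

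**What the plan says.** Under Quantitative data, the primary outcome analysis covers two quantities: "total adherence scores at end of follow-up as well as change in scores between baseline and follow-up will be compared using linear regression analysis". Neither is named as the deciding one. The same paragraph closes with a common error rate: "For all quantitative analyses a two-sided test of statistical significance will be used with an alpha level of 0.05".

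Covariate adjustment is conditional. If randomisation turns out unequal on centre size, geography, "or the centres belonging to a university hospital (yes/no), adjusted multivariable analysis will be performed". The baseline adherence score is not among these covariates.

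The baseline score will exist, because The interventions says that "baseline structure and process variables will be administered through the SWEDEHEART-CR registry at all CR centres".

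Sample size calculations gives the planning figures: "The mean adherence score was 30.8 (standard deviation [± 2.4]) out of a maximum available score of 39"; "23 out of possible 26 CR centres in each group (minimal drop-out is anticipated"); power of 80%; "An alpha value of 0.05"; and, as the result, "a difference of ± 2.0 in adherence score between centres in cluster B" and cluster C. For A versus B it assumes 14 of 17 centres per group, drawn from the lower two baseline tertiles, and a detectable difference of 2.5.

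The timeline ends the audit intervention early if an interim difference of at least 2.0 points is seen. It does not say whether that is a difference in final score or in change.

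**The concern.** Two primary contrasts without an order leave three questions open.

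- **Which result decides?** The two estimates differ by exactly the chance difference between arms at baseline. One can be significant, or cross the 2.0-point interim threshold, while the other does not.
- **What is the error rate?** Each test carries the full 0.05. If a significant result on either were read as success, the error rate per comparison would exceed 5%.
- **Is precision lost?** The number of centres is fixed, so the analysis is one of the few remaining sources of power. The final score makes no use of baseline. The change score subtracts it with a slope of 1 whatever the data show, and is noisier than the final score when the correlation is below 0.5. ANCOVA estimates the slope.

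**Working it through.** **Inputs.** From Sample size calculations: SD 2.4 (8 feasibility centres, cross-sectional), 23 per arm (B versus C), 14 per arm (A versus B), power 80%, alpha 0.05, taken as two-sided as in Quantitative data. The baseline/follow-up correlation r is not in the document; I assume 0.5-0.8. Baseline and follow-up SDs are taken as equal across all centres.

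**1. The plan's own figure.** Detectable difference = (1.960 + 0.842) × SD × √(2/n).
- B versus C: 2.80 × 2.4 × √(2/23) = 1.98, against the stated 2.0; normal-approximation power at 2.0 is 80.7%. (With the t distribution: 2.03 and 78.9%.)
- A versus B: 2.80 × 2.4 × √(2/14) = 2.54, against the stated 2.5.

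The stated power therefore matches an unadjusted final-score analysis. All figures below use the normal approximation.

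**2. Error rate if either contrast sufficed.** With equal SDs, the final-score and change-score tests correlate at √((1−r)/2). From the bivariate normal:

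| r | correlation of tests | P(at least one false positive) |
|---|---|---|
| 0.5 | 0.500 | 9.1% |
| 0.7 | 0.387 | 9.4% |
| 0.8 | 0.316 | 9.5% |

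At r = 0 it is 8.3%; two independent tests would give 9.75%. Simulated t-tests agree: 9.1% (r = 0.5) and 9.3% (r = 0.7) at 23 per arm, 9.2% and 9.4% at 14 per arm. With follow-up SD 0.7 or 1.3 times the baseline SD and r = 0.5-0.9, the range is 8.4-9.75%.

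**3. Disagreement.** The baseline difference between B and C has standard error 2.4 × √(2/23) = 0.71 points, which is the typical gap between the two estimates. At a true difference of 2.0 with 23 per arm, exactly one of the two tests is significant in about 19-22% of trials for r = 0.8-0.5.

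**4. Precision, B versus C.** Variance relative to the final score is 2(1−r) for the change score and 1−r² for ANCOVA. The detectable difference is 1.98 times the square root of that.

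| r | final | change | ANCOVA |
|---|---|---|---|
| 0.5 | 1.98 | 1.98 | 1.72 |
| 0.7 | 1.98 | 1.54 | 1.42 |
| 0.8 | 1.98 | 1.25 | 1.19 |

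Against the final score, ANCOVA saves 0.26 to 0.79 points; against the change score, 0.26 to 0.06.

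**5. Precision, A versus B.** Only the lower two baseline tertiles enter. Under bivariate normality with SD 2.4 in all centres, this truncates baseline at z = 0.431 and leaves a baseline variance of v = 0.468 of the full value. Relative variances become:
- final: 1−r²+r²v = 0.867 (r = 0.5), 0.659 (r = 0.8)
- change: 1−r²+(1−r)²v = 0.867, 0.379
- ANCOVA: 1−r² = 0.750, 0.360

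Multiplying 2.54 by the square roots gives detectable differences of 2.37-2.06 (final), 2.37-1.56 (change) and 2.20-1.52 (ANCOVA).

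In this restricted sample the two SDs are no longer equal. The covariance of final and change is 1−r²−r(1−r)v = 0.633 (r = 0.5) and 0.285 (r = 0.8), so the tests correlate at 0.73 and 0.57. The either-contrast error rate is then about 8.2-8.9%, slightly below the table in step 2.

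**The case against.** The strongest reply is that the inflated error rate depends on a rule the protocol never states. A reader might infer from two tests at 0.05 that the trial has a false-positive rate near 10% per comparison. The document does not support that: it does not say that either contrast suffices. If one were named primary, or both were required, the inflation would vanish. The endpoint definition, the power calculation and the interim rule all speak of the adherence score itself, which leans towards the final score, and an unshown analysis plan may rank the two. This stands, so the 9.1-9.5% is conditional.

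A reader might also infer that baseline is ignored altogether and that ANCOVA would cut the B versus C detectable difference from 1.98 to 1.19. That is also too strong. The change score already uses baseline and reaches 1.25 at r = 0.8. For A versus B, starting from 2.54 would overlook the restriction on baseline score.

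Finally, each unadjusted contrast is valid under randomisation, and the stated power fits the final-score analysis. That stands too. ANCOVA's advantage is a large-sample one, and the degrees of freedom spent matter somewhat at 14 per arm.

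What the reply does not remove is that the protocol itself places both contrasts under the primary analysis, with no order, and lists adjustment covariates that omit the baseline score.

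**Conclusion.** The point holds as one of clarity and efficiency and is a should-fix. The protocol fixes two unranked primary contrasts per comparison and does not use baseline in the most efficient way, although it is collected at every centre. The excess false-positive risk is about 4 percentage points per comparison, and only if success on either contrast is accepted. The precision gain from ANCOVA is substantial against the final score (13-40% of the detectable difference for B versus C: 0.26/1.98 to 0.79/1.98) and 13-5% against the change score (0.26/1.98 to 0.06/1.25). For A versus B it is about 7-26% against the final score (0.17/2.37 to 0.54/2.06).

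These sizes rest on an assumed r of 0.5-0.8, an SD of 2.4 from only 8 centres, equal SDs over all centres and, for A versus B, bivariate normality. That two contrasts are named without an order does not depend on any of these.

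**What to change.** Name one primary analysis for each comparison: linear regression of the end-of-follow-up adherence score on arm, baseline adherence score and randomisation stratum. Label the change-score analysis supportive, without a claim of its own. State that the 2.0-point interim difference refers to the estimate from the same model.

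The cost is wording plus about 3 degrees of freedom (1 for baseline, 2 for three strata), from 44 residual degrees of freedom with 23 centres per arm (46 − 2) or 26 with 14 per arm (28 − 2). No new data are needed. The change should be made before outcome data by arm are examined, because choosing between two primary results afterwards would not be credible.

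### Adjustment for the randomisation stratum depends on an undefined observed imbalance, so the primary model can omit the design factor and lose precision

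*Protocol article*

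**What the plan says.** Under Randomization, the article states "Centres will be randomized 1:1:1 to three clusters (A, B and C") and "Randomization will be stratified by geographical healthcare district (two districts in each stratum"). Six districts paired two by two give three strata.

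Under Quantitative data, the primary analysis is fixed as follows: "total adherence scores at end of follow-up as well as change in scores between baseline and follow-up will be compared using linear regression analysis". No covariate is named. The next sentence brings covariates in only on a condition: "In the case of unequal randomization concerning CR centre size", or on "geography (6 geographical districts in Sweden, two in each stratum"), or on university-hospital status, "adjusted multivariable analysis will be performed". The list therefore contains the factor used to stratify the randomisation.

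The section gives no threshold or test for imbalance and no time at which it is judged. It does not say whether the adjusted result replaces the unadjusted one or stands beside it. It applies the same methods to the short-term patient outcomes. No other section of the article puts the stratum in the model.

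**The concern.** Stratified allocation removes between-stratum variation from the treatment comparison. A model without the stratum still counts that variation as residual noise. The confidence interval is then wider than the design warrants, and the test rejects less often than its nominal 5%. A rule that adjusts for geography only when it looks unequal tends to leave the stratum out when stratification has done its job.

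For centre size and university status, the wording leaves open which model is primary, because nobody can say in advance what counts as unequal.

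Precision matters here. The number of centres is fixed, the comparisons rest on 23 and 14 centres per arm, and planned power is 80%. The article's Background also makes a geographical effect plausible: responsibility for local guideline implementation lies with 21 autonomous regions, and service delivery differs considerably between centres.

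**Working it through.** **Inputs from Sample size calculations.** "The mean adherence score was 30.8 (standard deviation [± 2.4]) out of a maximum available score of 39"; "23 out of possible 26 CR centres in each group" for B versus C, with detectable difference 2.0; 14 of 17 per group for A versus B, with detectable difference 2.5; power 80%, alpha 0.05 (two-sided, per Quantitative data).

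**Input not in the article.** R², the share of score variance explained by the three strata. I assume 0%, 10%, 20% and 30%.

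**Step 1: reproduce the plan's figures.** Detectable difference = (1.96 + 0.84) × SD × √(2/n), using the unrounded normal quantiles.
- n = 23: standard error 2.4 × √(2/23) = 0.708; detectable difference 1.98 (2.03 with the t distribution). Stated: 2.0.
- n = 14: standard error 2.4 × √(2/14) = 0.907; detectable difference 2.54 (2.64 with t). Stated: 2.5.

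The stated figures reproduce approximately, and they correspond to an unadjusted comparison.

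**Step 2: what leaving out the stratum does.** With balance inside each stratum, the true standard error is 0.708 × √(1 − R²), but the unadjusted model reports about 0.708. So:
- interval too wide by the factor 1/√(1 − R²): 1.05 at R² = 10%, 1.20 at 30%;
- real type I error ≈ 2 × [1 − Φ(1.96/√(1 − R²))]: at 10%, 1.96/0.949 = 2.07, giving 3.9%; at 30%, 1.96/0.837 = 2.34, giving 1.9%.

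**Step 3: simulation with t-based tests.** 40,000 trials per setting, SD 2.4, ordinary linear regression, arms balanced within three strata (8, 8 and 7 centres per arm for B versus C).

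| R² (assumed) | Type I error, no stratum | Type I error, with stratum | Power at 2.0, no stratum | Power at 2.0, with stratum |
|---|---|---|---|---|
| 0% | 5.1% | 5.2% | 79% | 79% |
| 10% | 3.8% | 4.9% | 80% | 83% |
| 20% | 2.7% | 4.8% | 81% | 87% |
| 30% | 2.0% | 5.1% | 82% | 91% |

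A separate simulation with 8,000 trials per setting agrees to within about 1.5 percentage points; at 30% it gives 83% and 91% power.

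For 14 per arm and 2.5 points, with 5, 5 and 4 centres per arm and stratum balance assumed, power without and with stratum is 76% and 76% at R² = 0%, 76% and 79% at 10%, and 79% and 89% at 30%.

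**Step 4: the conditional rule itself.** The article gives no cut-off, so an illustrative one was used that fires on size or university imbalance in about 28% of trials. With strata explaining 10–30% of variance and the other factors nothing, the rule gave type I error of 2.6–4.4% and power of 79–84%, against 83–91% with stratum always included. If an analyst took the better of the unadjusted and fully adjusted results, type I error was 5.0–6.5% over all settings run.

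**The case against.** **The trigger may well fire.** The article describes geography by six districts, while randomisation balances only three pairs. Assuming 13 centres per district and near-exact 1:1:1 balance within strata, some district differs by 3 or more centres between B and C in about 67% of allocations, and by 4 or more in about 36%. Size or university status can also trigger adjustment. Drop-out can disturb stratum balance, as can the restriction of A versus B to the lower two baseline tertiles. This stands: a reader might infer that geography will never be adjusted for, and the text does not support that.

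**The stratum effect is unknown.** At R² = 0% nothing is lost. This stands, so a wider standard error is conditional, not certain. The figures also concern the end-of-follow-up score. Stable regional differences would partly cancel in the change score, where the gain could be smaller.

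**The plan still meets its own power.** For B versus C, unadjusted power is 79–83%, close to or above the 80% planned. This stands: the loss is a forgone gain, not a shortfall against the stated design.

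**Model choice after the fact.** A reader might infer that the rule lets the result be picked. The trigger rests on allocation and centre characteristics, not outcomes, and Table 3 places randomisation in Q3 2023, so balance could be judged before follow-up scores exist. The article does not propose taking the better of two results, and even that would raise the error only to about 6.5%.

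**The adjusted analysis may be additional, and an SAP may settle details.** Possible. But the conditional rule is stated in this article, so the point concerns a stated rule and not an omission.

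**Conclusion.** The concern holds as a matter of precision and pre-specification. The article stratifies by geography and then makes adjustment for geography, centre size and university status depend on an imbalance it does not define. The design factor can thus drop out of the primary model, most likely when it is balanced.

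For B versus C with SD 2.4, 23 per arm and balance within strata, if stratum explains 10–30% of score variance the unadjusted test runs at a real type I error of about 4% to 2% and gives up about 3 to 9 points of power at a difference of 2.0. If stratum explains nothing, nothing is lost either way. These shares are assumptions.

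The documents do not support a claim of bias, or of a material rise in false positives. When stratification works, the error is on the conservative side. The trial remains valid under the current wording, but the rule buys nothing that unconditional adjustment would not give.

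**What to change.** In Quantitative data, and in the SAP if one exists:
- include the three-level randomisation stratum in the primary model for both comparisons and in the patient-level models, whatever the observed balance;
- delete the imbalance trigger;
- state in advance whether centre size and university status belong to the primary model, or to one named sensitivity analysis that is reported regardless of imbalance.

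The cost is a change of wording and 2 degrees of freedom. In the simulation this cost no visible power at 23 per arm, and 0.2 of a percentage point at 14 per arm, when stratum had no effect at all.
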